### Statistical analysis

Patients will be analysed according to the intention-to-treat protocol. General descriptive statistics on patient characteristic at baseline will be performed including factors such as gender and age. The primary outcome, DASH at one year, will be corrected for age and assessed using an analysis of co-variance (ANCOVA). Trends in DASH scores among the different time points will be assessed using a repeated measures ANOVA. The secondary outcomes; PRWE, quality of life (QoL SF-36), pain as indicated on a Visual Analogue Scale (VAS) and Range of Motion (ROM) will be analysed in a similar manner. The radiological outcome, number of conversions and complication rate will be determined using either a Fisher Exact of a Chi square test, depending on the order of magnitude of the results. Subgroup analyses with regard to DASH score will be performed for gender and age for each randomisation stratum.

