### Data collection and follow up

Baseline characteristics will be obtained after randomisation but before treatment takes place. During follow up patients will be asked to return to the hospital for follow up at; one, three and six weeks and three, six and twelve months, according to standard Dutch protocols [8]. During these visits patients will be asked about any complaints and/or complications and physical and radiological examination will be performed. For details, see Table 1. Procedures additional to standard care are highlighted.

**Table 1 T1:** Follow-up visits

**Follow-up at:**	**Tests:**
1 week	VAS, X-ray
3 weeks	VAS, X ray
6 weeks	VAS, ROM, Grip strength, QoL, X-ray, PRWE, DASH
3 months	VAS, ROM, Grip strength, QoL, X-ray, PRWE, DASH
6 months	VAS, ROM, Grip strength, QoL, X-ray, PRWE, DASH
12 months	VAS, ROM, Grip strength, QoL, X-ray, PRWE, DASH

Examinations additional to stand care are bold.

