### Sample size

This sample size calculation is based on the primary endpoint, the DASH score. The DASH score of an individual without any complaints of the wrist is 0. The mean DASH score after closed reduction and cast treatment after one year of follow up is 19 with a standard deviation (SD) of 18 [25]. This figure was measured in a patient population in which 72% suffered from a displaced extra-articular distal radius fracture. We assume that treatment with volar plating will decrease the DASH score which is achieved by conservative cast treatment by 15 points, from 19 to 4. Therefore at α = 0.05% and a power of 90%, with an estimated lost to follow-up of 10%, we would require 66 patients in total and 33 per treatment arm, to participate in the trial. This figure was calculated using the standard formula for means of superiority trials: n = [A + B]^2^ * 2 * SD^2^/DIFF^2^, where N = the number of patients required per arm, A the level of significance, B the power, SD the standard deviation of the primary outcome and DIFF the difference between the means. For safety measures and to correct for natural deaths, 45 patients in each arm will be included. From a separate study being conducted at the Academic Medical Centre Amsterdam and two other teaching hospitals, it was established that of the 703 distal radius fractures encountered in one year, 328 were an AO type A2 and A3. Therefore we estimate that we require a maximum of two years to include and follow up the patients in this trial.

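### The named repeated-measures ANOVA for DASH over time uses, in its standard form, only patients with every visit complete; a mixed model on all available visits would serve this secondary longitudinal analysis better

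*Protocol article*

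**What the plan says.** The Statistical analysis section of the protocol article makes four relevant statements.

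- Analysis population: "Patients will be analysed according to the intention-to-treat protocol".
- Primary analysis: "The primary outcome, DASH at one year, will be corrected for age and assessed using an analysis of co-variance (ANCOVA").
- DASH over time: "Trends in DASH scores among the different time points will be assessed using a repeated measures ANOVA".
- Other outcomes: after naming PRWE and SF-36, it says that "pain as indicated on a Visual Analogue Scale (VAS) and Range of Motion (ROM) will be analysed in a similar manner".

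Data collection and follow up sets visits at "one, three and six weeks and three, six and twelve months, according to standard Dutch protocols". Table 1 there lists DASH, PRWE, quality of life and range of motion at four visits (6 weeks, 3, 6 and 12 months) and VAS at six (adding 1 and 3 weeks).

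The Sample size section sizes the trial on one-year DASH, "with an estimated lost to follow-up of 10" per cent, and enrols 45 patients per arm.

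The Background hypothesises both a quicker recovery and better function at one year, while the stated aim is function at one year. The article does not say how incomplete visit sets are handled, nor whether a sphericity correction is used.

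**The concern.** The objection is to a method that the plan names, not to a missing detail. Classical repeated-measures ANOVA needs a full set of visits for each patient, so by default one missed visit removes that patient's other measurements too. Loss to follow-up is expected, and recovered or converted patients may plausibly attend differently from the rest. The patients left could then differ from those randomised.

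The primary ANCOVA looks only at one year. The repeated-measures analysis is therefore the only one named that can address speed of recovery. Its overall F test for visit by arm also does not by itself give the size of the arm difference at each visit, which is what that hypothesis needs.

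The within-patient tests (visit, and visit by arm) further assume sphericity, meaning equal variance of all between-visit differences. That is doubtful for visits spread from the first weeks to 12 months.

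**Working it through.** **1. The plan's own figure.** Inputs from the Sample size section: SD 18, a 15-point difference ("by 15 points, from 19 to 4"), power 90%, 10% loss. The significance level is printed as 0.05%, but the stated size fits two-sided 0.05.

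- n per arm = 2 × SD² × (1.960 + 1.282)² / DIFF² = 2 × 324 × 10.51 / 225 = 30.26.
- With 10% loss: 30.26 × 1.1 = 33.3, or 30.26 / 0.9 = 33.6, against the stated 33.
- Enrolling 45 and losing 10% leaves 40.5 per arm. Power = Φ(15 / (18 × √(2/40.5)) − 1.96) = Φ(3.75 − 1.96) = 96.3%.

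This calculation concerns one-year DASH alone, so the choice of longitudinal method does not touch it.

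**2. Complete cases from the stated loss only.** 90 × 0.90 = 81 patients. This is the only count that rests entirely on the article's figures.

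**3. Complete cases under assumed missed visits.** The article gives no missed-visit rate. Let m be an assumed independent miss rate per visit and k the number of visits; the complete share is (1 − m)^k, applied to 90 patients. The last column adds the stated loss on top, that is 81 × (1 − m)^k.

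| k | m | Share complete | Of 90 | With 10% loss on top |
|---|---|---|---|---|
| 4 (DASH) | 2% | 0.922 | 83 | 75 |
| 4 (DASH) | 5% | 0.815 | 73 | 66 |
| 4 (DASH) | 10% | 0.656 | 59 | 53 |
| 6 (VAS) | 2% | 0.886 | 80 | 72 |
| 6 (VAS) | 5% | 0.735 | 66 | 60 |
| 6 (VAS) | 10% | 0.531 | 48 | 43 |

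The VAS rows apply only if VAS is analysed by repeated-measures ANOVA and all six visits enter. Interventions places randomisation at one week, so the one-week VAS may be a pre-treatment value.

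**4. Sphericity.** The uncorrected visit-by-arm F test at nominal 5% was simulated with no treatment effect, 45 per arm and 20,000 runs per setting. First-order autoregressive correlation between successive visits was assumed.

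| Correlation | 4 visits: epsilon, rejection | 6 visits: epsilon, rejection |
|---|---|---|
| 0.5 | 0.86, 5.9% | 0.77, 6.9% |
| 0.7 | 0.77, 6.3% | 0.63, 7.5% |
| 0.9 | 0.68, 7.2% | 0.50, 9.1% |

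A separate simulation used four visits, assumed SDs of 22/20/18/18, one assumed correlation matrix within 0.3 to 0.8, 40 per arm and 10,000 runs. It gave 6.9% uncorrected and 5.1% with the Greenhouse-Geisser correction. The inflation is modest for DASH, and a routine correction removes it. That correction would not bring back patients dropped for a missed visit.

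**The case against.** The strongest reply is that the article names the method in one sentence and leaves the rest open. It does not say that patients with a missed visit are dropped, that imputation is ruled out, or that the F test is uncorrected. Such details are commonly left to a full protocol or SAP, which is not shown. This stands in part. The silence on missing data is no fault in itself, and a sphericity correction may well be intended. What remains is that the named method, taken in its standard form, is a poor match for four visits with expected loss.

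A reader might infer several stronger points that the documents do not support.

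- *That the plan contradicts its intention-to-treat statement.* In its core sense that term means analysis by allocated arm, which repeated-measures ANOVA can respect. Discarding usable data from randomised patients is in tension with the aim, not in contradiction with it.
- *That sphericity is part of that tension.* It bears on the error rate of the within-patient tests only, not on who is analysed and not on the between-arm main effect.
- *That the primary result is at risk.* It rests on a separate one-year ANCOVA.
- *That PRWE, SF-36, VAS and range of motion are certainly affected.* The sentence on them follows both the ANCOVA and the repeated-measures sentence and may mean either or both.
- *That complete-case analysis is biased whenever data are not missing completely at random.* It can also be valid when missingness depends only on covariates in the model.

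**Conclusion.** The point holds for the secondary longitudinal analysis of DASH, and for the other repeated outcomes if the ambiguous sentence includes them. On the article's own 10% loss, at most about 81 of 90 patients would contribute. The range of about 73 to 59 rests on assumed, independent miss rates of 5% to 10% per visit without further loss. All sphericity figures rest on assumed correlations and on an uncorrected test, and for four visits they amount to roughly 6% to 7% against a nominal 5%.

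The consequence is a weaker and possibly selective answer on speed of recovery, which is part of the stated hypothesis but not of the stated primary aim. The primary test and the sample size stand. This is an improvement worth making before analysis, not a flaw that threatens the main conclusion.

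**What to change.** In the Statistical analysis section, replace the repeated-measures ANOVA with a likelihood-based linear mixed model. Fit arm, visit, arm by visit and age stratum with an unstructured covariance across visits, by allocated arm, using every available visit. Report the arm difference in DASH with its 95% CI at 6 weeks, 3, 6 and 12 months. State whether PRWE, SF-36, VAS and range of motion follow this model, the one-year ANCOVA, or both. The primary ANCOVA needs no change on this account.

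The cost is a change of wording, standard software and slightly more analysis work, with no new data or patients. An unstructured covariance has k(k + 1)/2 parameters: 4 × 5 / 2 = 10 for four visits and 6 × 7 / 2 = 21 for six. The model is valid under missing at random, an assumption to be stated because the data cannot verify it. A patient with no measurement at any visit still contributes nothing.

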**Design:**

This single blinded randomised controlled trial will randomise between open reduction and internal fixation with a volar locking plate (intervention group) and closed reduction followed by plaster immobilisation (control group). The study population will consist of all consecutive adult patients who are diagnosed with a displaced extra-articular distal radius fracture, which has been adequately reduced at the Emergency Department. The primary outcome (functional outcome) will be assessed by means of the Disability Arm Shoulder Hand Score (DASH). Secondary outcomes comprise the Patient-Rated Wrist Evaluation score (PRWE), quality of life, pain, range of motion, radiological parameters, complications and cross-overs. Since the treatment allocated involves a surgical procedure, randomisation status will not be blinded. However, the researcher assessing the outcome at one year will be unaware of the treatment allocation. In total, 90 patients will be included and this trial will require an estimated time of two years to complete and will be conducted in the Academic Medical Centre Amsterdam and its partners of the regional trauma care network.

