## Background

Fractures of the distal radius account for an estimated 17% of all fractures diagnosed [1,2]. Two-thirds of these fractures are displaced and require reduction [3]. Although extra-articular distal radius fractures are considered to be relatively harmless, inadequate treatment may result in severely impaired function of the wrist [4,5]. The consequences of post-traumatic loss of function are comprehensive, both on individual and societal level, and have long been underestimated [6].

Several treatment modalities to obtain and maintain reduction exist and decision-making is mainly based on fracture type, region and surgeon’s preference [7]. Although good results have been described for both conservative and surgical management, the ideal treatment method remains unknown.

According to current Dutch guidelines, standard treatment for patients with displaced extra-articular distal radius fractures consists of closed reduction and cast immobilisation for four to six weeks [8]. Nevertheless, redisplacement occurs in up to 60% of cases and functional recovery is frequently poor [9-11]. If fracture redisplacement occurs, surgical reduction and fixation is the treatment of choice [8].

A well-established and widely applied surgical approach is open reduction and internal fixation (ORIF). This procedure involves surgical (open) fracture reduction and internal fixation by means of locking plates. Over the past years, the use of volar locking plates has become increasingly popular [12]. This type of osteosynthesis requires a relatively simple volar approach to the wrist, followed by fracture fixation using fixed angle implants [13]. The technique allows more accurate reduction and immediate stable fixation. Subsequent removal of the plate is rarely necessary [7,14]. The fracture stability allows for early mobilisation and may therefore result in an improved recovery of function [7,14]. By 1987 already, Dias et al. concluded that patients who were encouraged to mobilise their injured wrist from the start in a modified cast which only restricted extension, recovered function more quickly than those whose who were immobilised in a conventional plaster cast [10].

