### Interventions

All patients will initially be treated with closed reduction and cast immobilisation. This will take place under local anaesthesia by means of a haematoma block with 20 cc Lidocaine 1%. Closed reduction will be performed according to the Robert-Jones method [18]. This involves increasing the deformity first, then applying continuous traction and immobilising wrist and hand in the reduced position. Additional radiographs will be performed to verify the quality of the reduction (see Inclusion criteria). After this has been confirmed, the wrist will be immobilised according to Dutch guidelines: a dorsal splint for one week. Once informed consent is obtained, patients will be randomized at one week between open reduction and internal fixation with a volar locking plate, or continuation of cast immobilization.

The intervention group will be treated with open reduction and internal fixation with a volar locking plate. The surgery will be performed by a general, trauma or orthopaedic surgeon. In order not to disturb clinical practise, and to provide an accurate comparison of two treatment modalities as they are applied in clinical practise, no specific interval to surgery is prescribed. According to the current standard treatment protocol, antibiotic prophylaxis will be administered pre-operatively. The distal radius will be approached according to Henry, which involves an incision between the tendon of the flexor carpi radialis and the radial artery. The advantage of this approach is the possibility of an easy extension to the proximal or distal part of the forearm and the fact that the plate will be optimally covered by soft tissue [19]. Moreover, the median nerve is not at risk using this technique. After the fracture site is exposed, the fracture will be reduced and provisionally fixed with K-Wires and/or reduction forceps. An appropriate volar locking plate which best suits the anatomy of the wrist and the fracture type will be selected. Screw placement and fracture reduction will be confirmed intra operatively by radiographic images. Wound closure will be performed at the discretion of the surgeon using standard techniques and no post-operative fixation or immobilisation will be applied. During the first follow up visit at five to ten days, wound inspection will be performed. Patients will be instructed to use the affected extremity in daily activities as pain allows.

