The control group will continue treatment with cast immobilisation according to Dutch guidelines: a circular cast for another four weeks [8]. At one week and three weeks following initial immobilisation, radiographs will be performed in both groups to ensure that loss of reduction has not occurred. Loss of reduction is defined as: >15° dorsal or >20° volar angulation of the distal fracture fragment, >5 mm loss of radial height, or ≤15° radial inclination [8]. If this is the case, operative treatment will be offered. According to Dutch treatment standards, vitamin C 500 milligrams will be prescribed to all patients at initial presentation and for a duration of two months in order to prevent Complex Regional Pain Syndrome [8].

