### Secondary outcomes

• Rist pain and disability expressed as change on Patients-Rated Wrist Evaluation Score (PRWE). The PRWE is a validated tool for assessing functional outcome in patients with distal radius fractures [21]. This score was first described in 1998 by McDermid et al. [22] and developed by expert surveys. The PRWE is a 15-item questionnaire designed to measure wrist pain and disability in activities of daily living. The PRWE allows patients to rate their levels of wrist pain and disability from 0 to 10, and consists of three subscales: Pain, Function and Cosmetics.

• Quality of Life assessed using the Short Form–36 (SF-36^®^) questionnaire. The SF-36 is a validated multipurpose, short form health survey which contains 36 questions representing eight different health domains [23]. These domains are combined into a mental and physical component scale. From each domain, scores ranging from 0 to 100 points are derived, with lower scores indicating poorer quality of life.

• Pain as indicated on a visual Analogue Scale (VAS), in which 0 implies no pain and 10 the worst possible pain. Patients will be asked to give an estimation of the type and quantity of pain medication taken during all follow up visits.

• Patient satisfaction at one year by simply asking patients if they are satisfied with the result (yes/no).

• Range of motion of the wrist measured on both sides with a handheld goniometer.

• Prehensile grip strength as measured with a Baseline dynamometer.

• Radiological parameters: radial inclination, volar/dorsal tilt, communition, ulnar variance and radial length measured digitally in the Picture Archiving and Communication System (PACS) on standard posterior anterior (PA), lateral carporadial and lateral X-rays of the wrist. Radiographs will be obtained according to standardised procedures. PA radiographs with the shoulder in 90 degrees abduction, elbow in 90 degrees flexion and the wrist in neutral position; lateral X-rays with the shoulder in neutral position and elbow in 90 degrees flexion; and the lateral carporadial radiographs will be obtained by positioning the lower arm on a 20-25 degrees angled wedge.

• Rate of cross-overs

• Complications such as: loss of reduction, fracture malunion or non-union, wound and/or plate infection, tendon irritation and/or rupture, neuropathy and the occurrence of complex regional pain syndrome according to the criteria by Veldman et al. [24].

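### The between-arm test planned for conversions does not measure a treatment effect, whichever way the undefined term is read

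*Protocol article*

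**What the plan says.** The Statistical analysis section of the protocol article groups three outcomes under one pair of tests: "The radiological outcome, number of conversions and complication rate will be determined using either a Fisher Exact of a Chi square test". The choice between the two tests is left to the size of the results. This is the only place where the word conversions is used, and it is not defined.

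The outcome lists use another term. The Secondary outcomes section has "Rate of cross-overs", and the abstract ends its list with "range of motion, radiological parameters, complications and cross-overs". Neither gives a direction.

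The Interventions section describes one route by which treatment can change. It says that "radiographs will be performed in both groups to ensure that loss of reduction has not occurred", sets radiographic limits, and adds: "If this is the case, operative treatment will be offered". Of the other arm it says: "The intervention group will be treated with open reduction and internal fixation with a volar locking plate". On timing, "no specific interval to surgery is prescribed".

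The Background gives the only related rate: under cast treatment "redisplacement occurs in up to 60% of cases".

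**The concern.** In a two-arm trial, a Fisher exact or chi-square test on a count compares the arms, and its null hypothesis is equal event rates. That is useful only if both arms can have the event and the event means the same in each.

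Here one of these conditions fails on either reading. If a conversion is a move from cast to surgery, patients allocated to surgery cannot make it, and equal rates would mean that no cast patient is ever operated on. If a conversion is any departure from allocation, a cast patient counts when the cast treatment fails, and a plate patient counts when the operation is not done. The second event says nothing about how well plating works.

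What is at stake is interpretation. A small p-value could be read as fewer conversions thanks to plating when the definition of the endpoint produced it. The informative quantity, how often an adequately reduced fracture managed in a cast ends in surgery, is a proportion within one arm. A between-arm test does not estimate it.

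**Working it through.** **Plan's own figure.** There is none for this outcome: no conversion rate is assumed and no power is given for the test.

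**Inputs.**
- 45 patients per arm (Sample size section).
- Two-sided 5% level: assumed here, because no level is stated for secondary outcomes.
- Cast-arm conversion rates of 5% to 60%: all assumed. The 60% in the Background is an upper figure for redisplacement, not for operation.
- Plate-arm event rate: 0 if conversion means cast to surgery; 5% and 10% are assumed for the reading that also counts operations not done.

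**Step 1: smallest significant count, plate arm at zero.** For k of 45 against 0 of 45, the two-sided Fisher p-value is 2 × C(45,k) / C(90,k).
- k = 5: 2 × 1,221,759 / 43,949,268 = 0.056
- k = 6: 2 × 8,145,060 / 622,614,630 = 0.026

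The uncorrected chi-square statistic is 90k / (90 − k).
- k = 3: 270 / 87 = 3.10, p = 0.078
- k = 4: 360 / 86 = 4.19, p = 0.041

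Fisher's test therefore needs 6 conversions and chi-square needs 4. At 4 or 5 conversions, the choice of test decides the result. With 40 per arm (45 less about 10% loss) the thresholds are the same: Fisher p = 0.055 at 5 and 0.026 at 6; chi-square p = 0.040 at 4.

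**Step 2: chance of p < 0.05, plate arm at zero.** This is P(X ≥ 6) for Fisher and P(X ≥ 4) for chi-square, with X binomial(45, assumed rate).

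| Assumed cast-arm rate | Fisher | Chi-square |
|---|---|---|
| 5% | 0.02 | 0.19 |
| 10% | 0.29 | 0.67 |
| 15% | 0.69 | 0.92 |
| 20% | 0.91 | 0.99 |
| 30% | 0.997 | 1.00 |
| 60% | 1.00 | 1.00 |

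**Step 3: both directions counted.** Exact enumeration of two binomials, 45 per arm.

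| Cast to surgery | Plate arm not operated | Fisher | Chi-square |
|---|---|---|---|
| 20% | 5% | 0.48 | 0.63 |
| 30% | 5% | 0.86 | 0.92 |
| 30% | 10% | 0.58 | 0.69 |
| 60% | 10% | 0.999 | 1.00 |

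For a fixed cast-arm rate of 30%, Fisher's chance of significance drops from 0.997 to 0.58 as non-uptake in the plate arm goes from 0 to 10%. The p-value thus responds to how many plate-arm patients miss the operation, which is not an effect of plating.

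**Step 4: what an estimate would show.** As an illustration, 18 of 45 cast patients operated on is 40%, with an exact (Clopper-Pearson) 95% interval of 26% to 56%. The Fisher p-value against 0 of 45 is about 0.000001 and adds nothing to that.

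**The case against.** The strongest reply is that the article nowhere confines conversions to the cast arm. The listed outcome is cross-overs without direction. With no fixed interval to surgery, a patient allocated to a plate may stay in a cast. A two-way count has a well-defined null. This stands as to the validity of the test, and it means that the structural zero depends on the reading. It does not rescue the interpretation: equal counts of cast failure and of operations not done would not mean that the treatments perform equally.

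It can also be said that the radiographic check, and hence the offer of surgery, covers both groups as written. That is so. But surgery on a plate-arm patient still waiting is the allocated treatment, and surgery on one already plated is a re-operation. Neither is a change of arm.

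A reader might infer that the test is bound to be significant by design. The article does not support that. It gives no conversion rate, the 60% is an upper bound for redisplacement, and surgery is only offered. At assumed rates of 5% to 15%, Fisher's test would reach significance with probability 0.02 to 0.69.

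Finally, a condensed article may leave endpoint definitions and intervals to a fuller document, and nothing in it says that fewer conversions will be claimed as a benefit. Both are fair, and they limit the weight of the point. The test, however, is named in this text, so the choice is stated here and not merely omitted.

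**Conclusion.** The point holds in a limited form. The article names a two-group test for an outcome that it does not define and lists elsewhere under a different, undirected term. Read as the Interventions section describes it, the plate arm has a structural zero; read as any departure from allocation, two unlike events are compared. On both readings the p-value is not evidence about treatment effect, whether or not it falls below 0.05.

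How often a misleading significant result would arise cannot be fixed from the document. With zero plate-arm events, 45 per arm and Fisher's test at an assumed two-sided 5%, the chance is about 0.91 at a 20% conversion rate and about 1.00 from 30% upwards, but small to moderate at 15% or below. It is lower if plate-arm patients who are not operated on are counted too. A claim that conversion can occur only in the cast arm, or that significance is near certain, would go further than the text allows.

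This is one secondary outcome. The primary comparison of DASH at one year by intention to treat does not depend on it.

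**What to change.** In the Statistical analysis section, take the number of conversions out of the Fisher exact and chi-square tests, and use the same term as in the abstract and the Secondary outcomes section. State that cross-overs are reported by direction:

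- (a) the proportion of the cast arm operated on after loss of reduction;
- (b) the proportion of the plate arm that did not receive the allocated operation.

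Give each with an exact 95% confidence interval, and do not test one against the other.

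The cost is a change of wording and one lost p-value on a secondary outcome. Cross-overs are already a listed outcome. Loss of reduction is listed among the complications and checked by radiograph in both groups, so it keeps a between-arm comparison through the complication rate.

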### Inclusion criteria

• Patients ≥ 18 years and ≤ 75 years

• Extra-articular (AO type A) displaced distal radius fracture, as classified on lateral, posterior-anterior and lateral carporadial radiographs by a radiologist or trauma surgeon.

• Acceptable closed reduction obtained according to current Dutch guidelines [1].

•<15° dorsal or <20° volar angulation of the distal fracture fragment

•<5 mm loss of radial height

•≥15° radial inclination

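### Continuous radiological measurements are assigned Fisher exact or chi-square tests, with no categories fixed for that analysis

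*Protocol article*

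**What the plan says.** The Statistical analysis section of the protocol article divides the secondary outcomes into two groups. PRWE, SF-36, VAS pain and range of motion follow the DASH methods: ANCOVA corrected for age, and repeated measures ANOVA for trends. The second group gets tests for counts: "The radiological outcome, number of conversions and complication rate will be determined using either a Fisher Exact of a Chi square test". The choice between those two tests is made "depending on the order of magnitude of the results".

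Secondary outcomes defines the radiological parameters as "radial inclination, volar/dorsal tilt, communition, ulnar variance and radial length measured digitally" in the imaging system. It also gives an open list of adverse outcomes, beginning "Complications such as: loss of reduction, fracture malunion or non-union", and lists the rate of cross-overs as a separate item.

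Radiographic limits appear in two other places. Inclusion criteria sets the limits for an acceptable closed reduction, among them "≥15° radial inclination". Interventions defines loss of reduction, in connection with the one- and three-week radiographs, as ">15° dorsal or >20° volar angulation of the distal fracture fragment, >5 mm loss of radial height, or ≤15° radial inclination"; surgery is then offered.

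**The concern.** Fisher exact and chi-square tests compare counts across categories. Four of the five radiological parameters are angles or lengths, so following the plan as written means dichotomising them first. This costs power in a trial of 45 patients per arm. Unless the cut is fixed beforehand, it also leaves a choice that could influence the result. The article states this method explicitly, and the method does not match the type of data, so this is not a detail merely left for later. The same section already names a suitable method for the other continuous outcomes it lists.

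A secondary matter concerns the complication rate. Loss of reduction is among the listed complications and can also lead to conversion. If the complications are combined into one rate, a difference between arms could come largely from that single event, and a reader could not tell without a breakdown.

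**Working it through.** **Outcome type against planned test**

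| Parameter | Type | Does Fisher/chi-square fit directly? | Limit stated anywhere? |
|---|---|---|---|
| Radial inclination | continuous (degrees) | no | yes, but the two limits conflict at 15° |
| Volar/dorsal tilt | continuous (degrees) | no | yes, as angulation |
| Radial length | continuous (mm) | no | only as loss of radial height |
| Ulnar variance | continuous | no | none |
| Comminution | categorical | yes | not needed |

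At exactly 15° of inclination, a wrist is acceptable under Inclusion criteria and has lost reduction under Interventions. Neither set of limits is tied to the radiological outcome in the analysis.

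**Information kept after a cut**

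The plan gives no power figure for the radiological outcomes, so there is none to reproduce. For a normal variable cut so that a proportion p lies on one side, the large-sample efficiency relative to comparing means is φ(z_p)² / [p(1 − p)].

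- p = 0.5: 0.3989² / 0.25 = 0.637 (= 2/π)
- p = 0.2: 0.2800² / 0.16 = 0.490
- p = 0.1: 0.1755² / 0.09 = 0.342

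The Sample size section plans 45 per arm and 10% loss, leaving 45 × 0.9 ≈ 40. Multiplying 40 by these efficiencies gives about 25, 20 and 14 patients per arm. The 20% and 10% splits are assumptions.

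**The same loss expressed as power**

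The document gives no radiographic SDs, so the true differences of 0.5 to 0.8 SD are assumptions. The calculations use 45 per arm and two-sided 5%. The continuous comparison uses the noncentral t with noncentrality d√(n/2). The chi-square uses the normal approximation:

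Φ{[|p₁ − p₂| − 1.96√(2p̄(1 − p̄)/n)] / √([p₁(1 − p₁) + p₂(1 − p₂)]/n)}

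Fisher power is by exact enumeration.

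Example at d = 0.6, cut midway between the means: p₁ = 1 − Φ(0.3) = 0.382 and p₂ = 0.618. Chi-square power = Φ[(0.236 − 0.207)/0.102] ≈ 61%, against 80% for the continuous comparison.

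| Difference (SD) | Continuous | Chi-square, midway cut | Fisher, midway cut | Chi-square, cut 1 SD further out | Fisher, cut 1 SD further out |
|---|---|---|---|---|---|
| 0.5 | 65% | 47% | 37% | 34% | 24% |
| 0.6 | 80% | 61% | 52% | 45% | 35% |
| 0.7 | 91% | 75% | 66% | 57% | 47% |
| 0.8 | 96% | 85% | 78% | 68% | 59% |

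At the favourable cut the loss is about 11 to 19 percentage points with chi-square and 18 to 29 with Fisher.

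**Combined complication rate (illustration only)**

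The Background section gives redisplacement in cast as up to 60%. Assume no loss of reduction after plating, other complications of 15% in both arms, and independence. The cast arm's combined rate is then 1 − (1 − r)(1 − 0.15). With 45 per arm and the chi-square formula above:

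| Loss of reduction in cast (r) | Combined rate, cast v plate | Chance of a significant result |
|---|---|---|
| 10% | 24% v 15% | 17% |
| 20% | 32% v 15% | 48% |
| 30% | 41% v 15% | 78% |
| 40% | 49% v 15% | 95% |
| 60% | 66% v 15% | >99% |

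A combined rate could therefore differ through loss of reduction alone. How likely that is depends heavily on the assumed r.

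**The case against.** The best defence is that the radiological outcome, named in the singular beside conversions and complications, means a yes/no judgement of alignment. The named tests would then be valid, and limits for angulation, height and inclination exist in the article before any data. A condensed article may leave the derivation to a fuller document. This defence has weight: a reader might infer that the planned test cannot be run, or that cut-points will be picked after seeing the data, and the article supports neither inference. It does not remove the mismatch. The outcome is defined as a list of measurements. The Interventions limits serve to detect loss of reduction, say nothing of ulnar variance, and are not linked to the analysis.

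The efficiency figures assume normality, and the more extreme splits are not document figures. Both limits are accepted.

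On complications, a reader might infer that the plan pools loss of reduction into one tested rate, counts it again as a conversion, and so could declare plating safer merely because casts slip. The document does not go that far. The analysis sentence does not mention loss of reduction, and separate rates per complication are not excluded. An offer of surgery is not a conversion, and cross-overs are already a separate outcome. Redisplacement is a genuine harm of casting, named as such in the benefits and risks section. Removing it would drop one of the cast arm's own named risks while keeping the surgical ones.

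**Conclusion.** The point holds for the four continuous radiological measurements: the article assigns them a test for categories and fixes no categories for that analysis. At best, with a median split of a normal variable, about 64% of the information is kept, and less at more extreme cuts. In power terms the loss is material at this sample size, given the assumed 0.5 to 0.8 SD differences. Fisher or chi-square remains suitable for comminution, conversions and complications. The complication matter is secondary: it calls for a breakdown so that any difference can be attributed, not for a changed definition. Only secondary outcomes are involved; the DASH analysis and the sample size stand apart from this.

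**What to change.** Amend the Statistical analysis section as follows:

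- Analyse radial inclination, volar/dorsal tilt, ulnar variance and radial length each with the age-adjusted ANCOVA, and the repeated measures model across visits, as for the other continuous secondary outcomes. Report mean differences with 95% CIs.
- Keep Fisher exact or chi-square for comminution, conversions and complications.
- If a yes/no alignment endpoint is also wanted, state its limits before the data are examined. The passages in Inclusion criteria and Interventions that disagree at exactly 15° of inclination must be reconciled by the investigators first.
- Report loss of reduction on its own line alongside the other complications. It may stay in any combined rate.

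The cost is a wording change in the protocol or SAP. No new data are needed, because the measurements are already planned as numbers.
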